### Musculoskeletal fitness in children (secondary outcome)

Musculoskeletal fitness, in terms of handgrip strength, will be measured by an analog dynamometer (TKK 5825, Grip-A, Takei, Tokyo, Japan) validated in preschool-aged children [46]. Measurement of handgrip strength will be conducted at baseline and at 6 months follow-up by trained field workers to the nearest 0.1 kg on both dominant and non-dominant hands.

### Psychosocial functioning of children (secondary outcome)

The psychosocial functioning of children will be assessed by a parental report of the Strength and Difficulty Questionnaire (SDQ) which has been used extensively worldwide and validated also in Swedish settings [47]. Parents will be asked to fill in the SDQ and sleep questionnaire at both baseline and 6 months follow-up. The SDQ questionnaire uses a 3-point Likert scale to measure the children’s psychosocial strength and problems summarized into an emotional symptoms scale, conduct problems scale, hyperactivity scale, peer problem scale, and prosocial scale. All scales except for the prosocial scale are then summarized into a total difficulties score. The result for psychosocial functioning will be reported as the total difficulties score as well as separate scores on each of the scales mentioned above.

### Sleep of children (secondary outcome)

Sleep will be measured using a combination of 24 h accelerometry, a sleep time diary during periods of accelerometer measurements, and a parental questionnaire to reflect sleep quality during the past 6 months. All measurements for sleep will be conducted at baseline and 6 months follow-up. Sleep onset, sleep duration, and waking up will be determined by algorithms integrated in GGIR [48]. Appropriate algorithms for detection of sleep in children will be used. The sleep time diary included in the parental measurement week questionnaire consists of two questions regarding children’s wake up time and bedtime. In addition, parents will answer questions in SDQ and sleep questionnaire about children’s sleep duration and quality during the past 6 months and these questions are adapted from the validated Ages and Stages Questionnaire [49]. To minimize the burden of answering different questionnaires, the sleep quality questions were added to the SDQ questionnaire; therefore, the questionnaire is named SDQ and sleep questionnaire.

### Screen time in children (secondary outcome)

Children’s screen time, in minutes of screen time per day, will be reported by parents at baseline and endpoint during periods of accelerometer measurements in the parental measurement week questionnaire.

### Absence due to illness in children (secondary outcome)

Absence due to illness frequency and duration from 12 months prior to the intervention baseline and during the 6-month intervention period (18 months in total) will be collected from the City of Stockholm central preschool absence database, a database to which all parents of preschool children in Stockholm report all sick leave.

### Adiposity of children (secondary outcome)

Weight, height, and waist circumference will be measured, by trained field workers, at baseline and 6 months follow-up. All measurements will be conducted twice, and each measurement result will be recorded to the nearest 0.1 of the respective unit. Weight will be measured by validated scales (calibrated scale: VB2-200-EC, Vetek AB, Väddö, Sweden), and height will be measured by stadiometers (portable stadiometer: Seca 213, Seca, Chino, CA, USA). Weight and height will then be used to calculate body mass index (kg/m^2^), and children will be classified as normal weight, overweight, or obese based on body mass index criteria developed by Cole et al. [50]. Waist circumference will be measured at the level of the navel directly on the skin [51]. Due to the COVID-19 pandemic, field researchers are required to conduct the measurements outdoors; thus, the waist circumference measurement may be conducted over thin clothing in cold weather.

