### Adiposity of preschool teachers (secondary outcome)

Weight and height will be measured by validated scales (calibrated scale: VB2-200-EC, Vetek AB, Väddö, Sweden) and stadiometers (portable stadiometer: Seca 213, Seca, Chino, CA, USA), and waist circumference will be measured at the level of the navel directly on the skin [51]. Due to the COVID-19 pandemic, field researchers are required to conduct the measurements outdoors; thus, the waist circumference measurement may be conducted over thin clothing in cold weather.

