### Data collection and data management

Participants will be asked to wear an accelerometer for 7 consecutive days for measurement of physical activity at both baseline and the 6-month follow-up. The accelerometer will be distributed at the respective participating preschool. The participants’ height, weight, waist circumference, and grip strength will be measured by trained field workers at the time the accelerometer is distributed. These measurements will be conducted twice to ensure data quality. After the data collection, the above measurements will be manually typed into a database on servers within the Center for Epidemiology and Community Medicine, Stockholm County Health Care Area (SLSO). All data will be typed in by one field worker and double-checked by a different field worker. [name] will perform range checks for the collected data.

All questionnaires are digitized. Participants will receive a unique link for the questionnaires in the email address they provided in the informed consent. The questionnaires are collected through Webropol, which is a trustworthy tool used in Region Stockholm.

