### Statistical analysis

The baseline demographic characteristics of the participants will be summarized descriptively. Dropout participants’ characteristics will be explored by comparison to the non-dropouts. Fidelity and dose of implementation will be summarized as a score (fidelity × number of weeks of compliance). The change in PA levels and secondary outcomes, from pre- to post-intervention, will be analyzed with linear mixed-effect models (to allow both fixed and random effects) nested on the preschool level. The linear mixed-effects model can test several aspects of the study effects, e.g., effects over time inside a group, and groups against each other at a given time (e.g., intervention vs. control at 6-month follow-up). Subgroup analyses will be conducted to analyze the effect of the intervention in relation to socioeconomic aspects. Furthermore, we aim to explore if the COVID-19 pandemic has modified any implementation aspects of the intervention (via questionnaires on how various routines including outdoor time, hygiene aspects at preschools, homestay, and transportation mode to/from preschool have changed following the COVID-19 pandemic).

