## Trial status

The trial was prospectively registered at clinicaltrials.gov with reference number NCT04569578. That is, the trial protocol was finalized and published before any recruitment or data collection took place. By the time of submission to *Trials*, the recruitment of the participants had been completed (recruitment period: 2020-09-23- 2021-07-02) and the data collection/study visit was ongoing. We were unable to submit the protocol to Trials before recruitment as the COVID-19 pandemic drastically increased the resources required to recruit participants, resulting in a delay of submission. Important changes to the protocol, if any, will be communicated to the journal and trial registry. Until May 2023, no change has been made to the trial protocol as pre-registered at ClinicalTrials.gov.

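### Waist may be taken on skin or over thin clothing according to the weather, so the method can differ between baseline and 6 months in an outcome analysed as change

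*Protocol article*

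**What the plan says.** The section on adiposity of children gives the standard method: "Waist circumference will be measured at the level of the navel directly on the skin". It then explains that, under COVID-19, "field researchers are required to conduct the measurements outdoors", and draws the consequence: "thus, the waist circumference measurement may be conducted over thin clothing in cold weather". The section on adiposity of preschool teachers repeats the exception: "field researchers are required to conduct the measurements outdoors; thus, the waist circumference measurement may be conducted over thin clothing in cold weather".

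On timing, the children's section states: "Weight, height, and waist circumference will be measured, by trained field workers, at baseline and 6 months follow-up". The data collection section ties body measurements to the handing out of accelerometers, and on place it says: "The accelerometer will be distributed at the respective participating preschool". The trial status section gives the "recruitment period: 2020-09-23- 2021-07-02".

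The statistical analysis section sets the estimand for waist along with the other secondary outcomes: "The change in PA levels and secondary outcomes, from pre- to post-intervention, will be analyzed with linear mixed-effect models". It adds that the model can test time effects within an arm as well as differences between arms.

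The article gives no temperature at which clothing is allowed and no requirement to use one method at both visits. The limitations in the discussion cover several COVID-19 effects but not this one.

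**The concern.** A change score is clean only if both readings are taken in the same way. Here the weather on the day decides the method, and the two visits are 6 months apart. If a child is measured on skin first and over clothing later, the change is too large by the thickness of the clothing. In the reverse order it is too small by the same amount. Taking each measurement twice at a visit does not help, because both readings would share the method.

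Measurement takes place outdoors at the preschool, so children of the same preschool are likely to meet similar conditions. An offset that they share does not average out over the children of that preschool; it behaves like extra variation between clusters. At stake are the reported change within each arm and the precision of the arm comparison for waist. Precision matters here because the hypothesis section expects no effect on adiposity, and a null result is informative only if its interval is narrow.

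**Working it through.** **No figure to reproduce.** The documents give no waist SD, ICC, effect size, power or clothing offset. The size below is an illustration on assumed values.

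**Can the method switch?** Recruitment ran from late September 2020 to early July 2021, so baseline visits may have fallen in most seasons. Adding 6 months pairs a January baseline with July, where a switch is likely, and an April baseline with October, where it may not occur. Switches can go in either direction.

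**Inputs from the documents (recruitment text).** Preschools with baseline data: 124, or 62 per arm at 1:1. Children per preschool: m = 3775/127 = 29.7.

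**Assumed inputs.** SD of waist change 2 cm (3 cm as a check); ICC of change 0.05; clothing offset c = 0.5, 1 or 2 cm; share of preschools switching, in one direction, p = 0.5 (0.25 as a check).

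**Model.** Observed change = true change + c × S, where S = 1 if the preschool switched and 0 otherwise.

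- Variance of a preschool mean without switching: V0 = SD² × (ICC + (1 − ICC)/m) = 4 × (0.05 + 0.95/29.7) = 0.328.
- Added variance from switching: A = c² × p × (1 − p).
- SE of the arm difference = √(4 × (V0 + A)/124).

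**Results at SD 2 cm, p = 0.5**

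| Offset c | A | SE (cm) | Ratio to no switching | 95% half-width (1.96 × SE, cm) |
|---|---|---|---|---|
| none | 0 | 0.103 | 1.00 | 0.20 |
| 0.5 cm | 0.0625 | 0.112 | 1.09 | 0.22 |
| 1 cm | 0.25 | 0.137 | 1.33 | 0.27 |
| 2 cm | 1.00 | 0.207 | 2.01 | 0.41 |

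**Sensitivity of the ratio at c = 1 cm**

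- ICC 0.02: 1.48. ICC 0.10: 1.22 (both with m = 30).
- SD 3 cm: SE from 0.154 to 0.178 cm, ratio 1.16.
- p = 0.25: ratio 1.25.
- A quarter of preschools switching each way: A = 0.5 × c² = 0.5, so the ratio is √((0.328 + 0.5)/0.328) = 1.59 and the SE is 0.16 cm. With c = 2 cm, A = 2 and the SE is √(4 × 2.328/124) = 0.27 cm.

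**Within-arm change.** With one-directional switching, the mean change in an arm shifts by p × c. At p = 0.5 that is 0.25, 0.5 or 1.0 cm for the three offsets; at p = 0.25 it is half as much. At c = 1 cm and p = 0.5, the SE of one arm's mean is √(0.578/62) = 0.097 cm, so the shift of 0.5 cm is about five standard errors. Balanced switching in both directions would cancel this shift but not the added variance.

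**Between-arm difference.** The shift p × c has the same expectation in both arms, so its expected contribution to the difference is zero. What remains is chance imbalance, with SD √(4A/124) = 0.045, 0.09 or 0.18 cm at p = 0.5. This is already included in the SEs above.

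**The case against.** The strongest reply is that the article declares the departure and its cause, and that recording the method or using it in a model is a matter for a measurement manual or analysis plan that is not shown. That is fair as to recording. It does not dispose of the point, because the article itself states a rule that permits two methods for an outcome it analyses as change.

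The reply is also right on several limits. Every driver of the size is assumed, and with thin clothing the offset may be at the low end, where the loss is about 9%. The trial has many clusters, so a large percentage increase still leaves a small SE. Waist is one measure within one of many secondary outcomes. If visits were grouped by district and the model adjusted for district, part of the noise would be absorbed; the article does not state such an adjustment.

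A reader might infer three stronger things that the documents do not support:

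- **That switching pushes the arm comparison towards no effect.** Allocation follows baseline, is 1:1 within district, and assessors are blinded. Weather does not depend on allocation, so an additive offset widens the interval and does not shrink the estimate.
- **That BMI is exposed in the same way.** The clothing exception names waist only, and nothing is said about what is worn for weighing.
- **That whole preschools certainly switch because the visits fall in opposite seasons.** The article gives recruitment dates, not visit dates; an autumn and spring pair may use one method; and nothing says that all children of a preschool are measured on one day. The retention section offers further chances to those who miss a measurement.

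**Conclusion.** The point holds as a minor flaw in a stated rule. Waist can be measured by different methods at the two visits, and the analysis is of change. Within-arm change in waist can be biased, by 0.5 cm in the illustration with a 1 cm offset and half of preschools switching one way. The arm comparison is not expected to be biased; it loses precision. On the stated assumptions the SE rises by about 9% at 0.5 cm and 33% at 1 cm, and it is still only about 0.2 cm at 2 cm. It would be larger, 0.27 cm at 2 cm, if half of preschools switched with equal numbers in each direction. These sizes rest on an assumed SD, ICC, offset and switching share, and on the inference that children of one preschool tend to share conditions. The primary outcome and the sample size are untouched.

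**What to change.** For children and teachers alike:

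1. Record skin or clothing for each waist measurement at every remaining visit. Recruitment was complete when the article was submitted, so for baselines already done take the method from field records, or use visit date as a proxy.
2. At follow-up, use the method that was used at baseline where feasible.
3. Include method switch as a covariate in the waist change model, coded with its direction (skin to clothing, clothing to skin, or the same), since the two directions have opposite signs.
4. Add a sensitivity analysis restricted to pairs measured by the same method.
5. Report within-arm change in waist only with this adjustment, or with a caution.

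The cost is one field on the form, one covariate, and some follow-up waists taken over thin clothing when skin measurement would have been possible. The same-method analysis will also be smaller than the main one.

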### Demographic information, children, and parents (descriptive)

Information on the age and sex of parents of the participating children will be derived from the personal registry number provided upon the consent of participation. Parents will also, at baseline, be asked to complete a descriptive information questionnaire including questions regarding their education level, occupation, country of birth, height, and weight.

### Children’s PA opportunities outside preschool time (process outcome)

Children’s PA opportunities including participation in organized sports and active transport to/from preschool will be assessed via parental measurement week questionnaire (during the weeks of accelerometer measures at baseline and 6 months follow-up). Parents will be asked about the time, duration and type of organized sports, and mode of transportation to/from preschool. In addition, parents will also answer an active transport questionnaire at baseline and 6 months follow-up regarding children’s general frequency of active transport, mode of transport, parental perception of the distance, and condition of transportation route during the past 6 months. Moreover, several parental practices (outdoor time during the weekend, parental perception of PA, parental PA levels, and active play with parents) which could potentially influence children’s daily PA levels will also be assessed by questions included in the parental questionnaire.

### Parental evaluation of the project and interview (process outcome)

A parental evaluation questionnaire will be distributed to parents of all participating children at 6 months follow-up. This evaluation questionnaire includes the parental rating (5 score scale) and open-ended questions on information quality, communication and perception of study influence, and experiences of study participation. Parents have the opportunity to report any unintended adverse effects of the intervention in this instrument. These questions will be used in qualitative analysis of potential facilitators and barriers of the study. At the end of this questionnaire, parents will be asked whether they want to participate in an interview to further explore the experience, influence, and potential of the study.

### Physical activity levels, sedentary time, and sleep in preschool teachers (secondary outcome)

Similar to children’s PA levels, ST, and sleep, these variables in teachers will also be measured objectively using triaxial GT3X+ accelerometers [39]. Preschool teachers will wear the accelerometer, on the non-dominant wrist, for 24 h during 7 consecutive days at baseline and 6 months follow-up. Minutes in total PA, MVPA, LPA, ST, and total steps during the preschool time, outside preschool time, and during the whole day will be reported for teachers. Sleep in preschool teachers will also be analyzed using 24-h accelerometry. Setup and analysis of accelerometer data will be performed following validated age-specific criteria and recommendations [39].

### Musculoskeletal fitness of preschool teachers (secondary outcome)

The method to assess musculoskeletal fitness in children will be used also for preschool teachers. Musculoskeletal fitness in terms of handgrip strength will be measured by an analog dynamometer (TKK 5825, Grip-A, Takei, Tokyo, Japan). Measurement of handgrip strength will be conducted at baseline and at 6 months follow-up by trained field workers and recorded to the nearest 0.1 kg on both dominant and non-dominant hands.

### Sick leave in preschool teachers (secondary outcome)

Sick leave frequency and duration from 12 months prior to the intervention baseline and during the 6-month intervention period (18 months in total) will be collected from the City of Stockholm central preschool absence database.

### Adiposity of preschool teachers (secondary outcome)

Weight and height will be measured by validated scales (calibrated scale: VB2-200-EC, Vetek AB, Väddö, Sweden) and stadiometers (portable stadiometer: Seca 213, Seca, Chino, CA, USA), and waist circumference will be measured at the level of the navel directly on the skin [51]. Due to the COVID-19 pandemic, field researchers are required to conduct the measurements outdoors; thus, the waist circumference measurement may be conducted over thin clothing in cold weather.

### Demography of preschool teachers (descriptive)

The age and sex of the preschool teachers will be derived from their personal registry number provided upon consent to participate in the study.

### Preschool policy and environmental characteristics (process outcome)

Preschool environmental/organizational characteristics such as available play equipment, playground characteristics, current policies, and working practices will be assessed by the validated Environment and Policy Evaluation and Observation as a Self-Report Instrument (EPAO-SR) [52]. The full EPAO-SR contains both PA and nutrition components in three surveys: Staff General, Director General, and Staff Daily respectively. A combination of Staff General and Director General surveys with only PA subscales will be used in the current study to access the classroom physical environment such as the amount of space for active play, preschool’s physical environment in terms of size and features of the preschool playground and routines, as well as policy regarding physical activity. The preschool playground characteristics and size will be double-checked and measured objectively via spatial mapping using publicly available satellite imagery (e.g., Google maps). Preschool-level routine screen time will be reported by preschool teachers in intervention preschools weekly through the intervention weekly follow-up questionnaire and via the validated EPAO-SR. [52] The use of EPAO-SR is important to identify what policies/practices that are in place prior to the intervention, and to assess if any other preschool environmental/organizational changes take place during the intervention period. It is also a crucial tool to measure the extent of any contamination by the intervention to the control preschools.

### Implementation of the policy package (process outcome)

Fidelity and dose of the implemented policy package will be documented through a weekly follow-up questionnaire, answered by preschool staff, throughout the intervention period. The extent to which the intervention can be normalized into preschool staff’s regular practice will be assessed through the validated [53] No-MAD questionnaire (an instrument for assessing implementation work based on normalization process theory) [54] at 6 months follow-up.

### Preschool teachers’ evaluation of the project (process outcome)

Communication, acceptance, facilitators, and barriers for implementation will be assessed through teachers’ evaluation questionnaires provided by all participating preschool teachers. At the end of the teachers’ evaluation questionnaire, preschool teachers will be asked whether they are willing to participate in focus groups and interviews. Focus groups and interviews with preschool personnel will also be undertaken post-intervention to collect more in-depth perspectives regarding the adequacy of the intervention, the feasibility of implementation, and suggestions for improvements. These qualitative discussions will generate rich data regarding the logistical challenges and the strengths and weaknesses of the intervention that could be missed in questionnaires. An experienced moderator, using a semi-structured interview guide, will facilitate the discussions. Sample questions will include:*What challenges did you experience when implementing the intervention?**What solutions did you undertake to deal with these challenges?**What characteristics of the intervention do you feel were most appropriate for increasing PA participation among preschoolers?*

Focus groups and interviews will be audio-recorded and transcribed verbatim.

